### Experimental paradigms

Identical to the pilot study, CBM-I training will be achieved via the Ambiguous Scenarios Task [46] modified for pain research by Jones and Sharpe [10]. Assessments of interpretation bias will be made via the test phase of the Ambiguous Scenarios Task and the Sentence Generation task. New to this main experimental study, the probe-position version of the Visual-Probe Task will be used to assess attentional biases for symbolic linguistic stimuli. Specifically, nine sensory-pain and neutral words pairs matched on length and length and Kucera–Francis written frequency [84] will be included (unique to this paradigm and not included in the Sentence Generation Task), which have been validated and used in our former research [62] (Table 4). The task will begin with eight practice trials featuring random letter strings as stimuli. This will be followed by a single block of 64 experimental trials, each of which features one sensory-pain and one neutral word pair. Each trial will begin with a fixation cross in the centre of the screen for 500ms, followed by a randomly selected word-pair presented vertically (i.e., one above the initial fixation cross, the other below) for either 500ms or 1250ms. Immediately after the disappearance of the word-pair, a visual-probe will be randomly displayed in either the upper or lower location replacing one of the former words. Participants must indicate the location of this probe as quickly as possible, using a two-button response-box (with ‘U’ and ‘L’ labels for upper and lower respectively) to provide their response. Following a randomly determined inter-trial interval of either 1000 or 1500 ms, the next trial will begin with the display of the initial fixation cross. The two stimuli presentation times will be applied in a randomised order over all trials. Each of the eight word-pairs will be presented eight times; four times for 500 ms and four times for 1250 ms. Within each exposure duration, each sensory-pain word will appear twice in the upper location and twice in the lower location. The probe location (upper or lower) will be counterbalanced across both locations, resulting in an equal number of congruent (probe replacing the sensory-pain word) and incongruent (probe replacing the neutral word) trials. This task will take approximately 15 minutes to complete. Also new to this main experimental study, a pen and paper version of the free recall task will be used to explore memory biases. Participants will unexpectedly be given two minutes to write down as many words as they can remember from the sentence generation and visual-probe tasks.

**Table 4 pone.0318296.t004:** Linguistic stimuli to be used in the visual-probe task.

Sensory-pain words	Neutral words
Throbbing	Autograph
Hurting	Surname
Stabbing	Creation
Painful	Stadium
Harmful	Auction
Aching	Volley
Uncomfortable	Refrigeration
Sore	Echo

### Quantitative sensory testing

#### Pain threshold measurement.

A similar procedure to the pilot study will be followed to assess each participant’s individual pain threshold, although in additional to heat pain thresholds cold pain thresholds will also be assessed the TSA-II previously described For both hot and cold trials the thermal stimulus will increase by 1°C/second from its baseline temperature of 32°C until the participant indicates the very first moment they feel the temperature as painful by pressing the left mouse button. The thermal stimulus has upper and lower safety limits of 53°C and 0°C. The thermal stimulus decreases by 8°C/second back to baseline temperature. Three hot and three cold trials will be conducted, with a 10-second inter-trial interval. The pain threshold measurement will take approximately 10 minutes.

#### Interpretation of somatosensory sensations assessment.

In addition to ambiguous heat stimuli discussed previously, the main experimental study will also assess interpretation of ambiguous cold stimuli administered to the non-dominant hand using the TSA-II. Specifically, cold stimuli at 60%, 80%, 100%, 120% and 140% of an individual’s cold pain threshold will be presented three times each, in a random order set across participants. Percentage threshold temperature values exceeding the safety limits of the TSA-II will be capped at 0°C (i.e., the TSA-II’s safety limits). Each cold trial will begin with the thermal stimulus decreasing from baseline temperature at a rate of 1°C/second until reaching the target temperature. The target temperature will be held for three seconds before returning to baseline at a rate of 8°C/second. At this point, participants will rate via pen and paper visual analogue scales the intensity (from 0 no sensation to 100 most intense pain you can imagine), and the unpleasantness (from 0 not unpleasant at all to 100 extremely unpleasant) of the stimulus. The fifteen cold trials will be presented consecutively with a 10 second inter-trial interval. The order of heat and cold pain trials will be randomised across participants, with the thermode removed for three minutes between each block of trials. This task will take approximately 20 minutes to complete

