The results of these two studies suggest that patterns of interpretation bias can be modified in healthy individuals using the Ambiguous Scenarios Task, which can subsequently impact performance on the cold pressor task. When deciding the point at which to report their level of pain threshold and tolerance, participants must by necessity interpret somatosensory sensations. Sensations around the pain threshold are likely to be ambiguously painful, sometimes interpreted as painful and sometimes as non-painful to the same individual, which has been proposed as a zone of uncertainty [12]. It is currently unclear whether CBM-I has a greater influence on interpretation of stimuli under or over the pain threshold, although the cold pressor task as used in former CBM-I research [10,11] does not allow for investigation of this question, which requires precise and fast administration of stimuli around each participant’s individual pain threshold. Experimentally delivered thermal stimuli administered via computerised thermal neurosensory analyser allows for testing of such hypotheses, as all aspects of the thermal stimulus presentation can be precisely controlled, including target temperature, duration of the thermal stimulus, and stimulation rates (i.e., the speed with which the target temperature is reached).

The primary aim of the main study detailed in this protocol is to investigate the effect of pain-related CBM-I on the interpretation of ambiguous somatosensory stimuli explored via a novel paradigm developed specifically for this investigation. Healthy, pain-free participants will be recruited as they are less likely to have pain-related cognitive biases than individuals with chronic pain [3,13]. This makes it possible to train such biases toward pain-related interpretations, as demonstrated in previous research [10]. To inform the development of this protocol, a pilot study was conducted to test the experimental methods and procedure and to establish study effect sizes. This was conducted in line with the NIHR, which defines pilot studies as ‘a smaller version of the main study used to test whether the components of the main study can all work together’[14] and which focuses on the processes to be followed in the main study to ensure they will run smoothly [15]. The methods and results of this pilot study will be presented first, followed by a discussion of insights gained and amendments made to the final protocol for the main experimental study.

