#### Sentence generation task.

This is a direct measure of interpretation bias, which has been successfully implemented in previous research from our research group [44,45]. The task included 18 experimental trials featuring nine ambiguous sensory-pain and nine ambiguous neutral stimuli [44]. Trials were presented in a new randomised order for each participant. Each trial began with a fixation cross for 1000ms. A single word replaced the cross, presented in size 40 Times New Roman font which remained on the screen until the end of the trial. Participants read the word and used a keyboard to type a single sentence featuring the word once. Text appeared in size 18 Times New Roman font below the experimental word as the participant typed. Backspace and delete keys were used to correct spelling mistakes or make amendments as necessary, and the F12 key was used submit the response. The next trial began after 120 seconds if no response was submitted. Trials followed one another automatically, with all 18 trials presented in a single block. Two practice trials were initially presented to familiarise participants with the requirements of the task, featuring the words *running* and *dancing*. This task took approximately 15 minutes to complete.

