#### Interpretation of somatosensory sensations assessment (ISSA).

This is a novel paradigm developed specifically for this study. Heat stimuli were administered to the non-dominant hand using the TSA-II. Stimuli were presented at 60%, 80%, 100%, 120% and 140% of an individual’s heat pain threshold three times each, in a random order set across participants, which was calculated individually for each participant using an app created in R-Shiny [48] (Fig 1; available at https://[name].shinyapps.io/temp_calculations_app/). Percentage threshold temperature values exceeding the safety limits of the TSA-II were capped at 50°C. Each trial began with the stimulus increasing from baseline temperature at a rate of 1°C/second until reaching the target temperature. The target temperature was held for three seconds, before returning to baseline by 8°C/second. At this point, participants rated, on pen and paper visual analogue scales, the intensity, from 0 (no sensation) to 100 (most intense pain you can imagine), and the unpleasantness of the heat stimulus, from 0 (not unpleasant at all) to 100 (extremely unpleasant). The fifteen heat trials were presented consecutively with a 10 second inter-trial interval. This task took approximately 10 minutes to complete.

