### Self-report measures

The following self-report measures will be administered in a newly randomised order for each participant: Anxiety Sensitivity Index-3 (ASI-III) [23]; Somatosensory Amplification Scale (SSAS) [32]; Fear of Pain Questionnaire– III (FoP-III) [34]; Pain Catastrophising Scale (PCS) [37]; Beck Depression Inventory-II (BDI-II) (Beck, Steer, & Carbin, 1988); Intolerance of Uncertainty Scale-12 Item (IUS-12) [81]; State-Trait Anxiety Inventory (STAI) [20]; Edinburgh Handedness Questionnaire – Short Form [40]. A demographic questionnaire will also be administered assessing sex, occupation, level of education, personal pain experiences (including number of headache days per month, for females their current phase of menstrual cycle) and prevalence of chronic pain among close relatives. The IUS-12 [81] is new for this main experimental study. This scale includes 12 items assessing an individual’s inclination to find uncertain situations unpleasant. Items are rated on a five-point scale ranging from 1 (Not at all characteristic of me) to 5 (Entirely characteristic of me). Total scores range from 12 to 60, with higher scores indicating greater intolerance of uncertainty. The IUS-12 has demonstrated excellent internal consistency (.91) [81] and acceptable test-retest reliability ((*r* = .77) [83]). Overall, the questionnaires will take approximately 25 minutes to complete.

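### The ISSA trials appear to run in one random sequence shared by all participants, which partly confounds stimulus level with trial position and can distort the under- versus over-threshold comparison, though not the group difference itself

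*Protocol article*

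**What the plan says.** In the main study, cold stimuli at five percentages of the individual threshold "will be presented three times each, in a random order set across participants". The heat block carries over from the pilot, where the same phrase is used and the sentence runs on: "in a random order set across participants, which was calculated individually for each participant using an app created in R-Shiny".

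Trials within a block follow each other closely: "The fifteen cold trials will be presented consecutively with a 10 second inter-trial interval". The order of the two blocks does vary: "The order of heat and cold pain trials will be randomised across participants".

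For other tasks the article states individual randomisation outright. For the Sentence Generation Task: "Trials were presented in a new randomised order for each participant". For the questionnaires, which "will be administered in a newly randomised order for each participant", likewise.

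The Introduction motivates the thermal analyser with an open question: "It is currently unclear whether CBM-I has a greater influence on interpretation of stimuli under or over the pain threshold". Hypothesis 1, however, is only a group difference for stimuli around the threshold. The analytic plan names t-tests and mixed-design ANOVAs. ISSA ratings are averaged per level, as in the pilot, and no term for trial position or preceding stimulus is named.

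**The concern.** If the sequence is drawn once and used for everyone, each level always occupies the same three positions in the block and always follows the same stimuli. With 15 trials there are 14 transitions, so at most 14 of the 25 possible level-to-level transitions can occur.

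The question of where training acts more strongly is answered by comparing the group difference across levels. A training effect that fades during the block would look weaker at levels that happen to come late and stronger at those that come early. A carry-over from the preceding stimulus that differs between arms would act in the same way. Recruiting more people does not help, because all of them share the imbalance.

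Some fading is plausible on the authors' own account: they moved the ISSA to directly after training so that intervening bias tasks could not weaken the effect. They give no figure for how fast it fades.

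**Working it through.** **1. Which reading?** The ISSA wording differs from the explicit per-participant wording used for the Sentence Generation Task and the questionnaires. The pilot's clause about individual calculation could refer to the order or to the temperatures. The Fig 1 caption and the Discussion describe the app as working out trial temperatures from the individual threshold, and neither describes it as drawing an order. One shared sequence is therefore the likelier reading, but it is not certain.

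**2. The plan's own figure.** With f = 0.244, N = 134 and two groups, the noncentrality is 134 × 0.244² = 7.98. Power with 1 and 132 degrees of freedom is 0.801 (0.798 at N = 133). The stated sample size reproduces and is not in question. It corresponds to d = 2 × 0.244 = 0.488 for a group difference.

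**3. Imbalance in one shared sequence.** Let D be the mean position of the six over-threshold trials (120% and 140%) minus that of the six under-threshold trials (60% and 80%). Positions 1 to 15 have variance 15 × 16/12 = 20, so SD(D) = √[20 × (1/6 + 1/6)] = 2.58 positions. Simulating 100,000 random orders confirms this and gives, for the absolute value of D, a median of 1.83, a 90th percentile of 4.33 and a 95th percentile of 5.0. With an own order for each of 134 participants, the average imbalance would have an SD of only 2.58/√134 = 0.22.

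**4. False over-minus-under difference.** Assumption, not in the documents: the training effect is equal at every level and falls linearly by a fraction L over the block. The false difference, as a share of the initial effect, is |D| × L/14. With L = 0.5:
- median order: 1.83 × 0.5/14 = 0.065, about 7%
- 90th percentile: 4.33 × 0.5/14 = 0.155, about 15%

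Taking the initial effect as d = 0.488, these are 0.03 and 0.08 SD.

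**5. Type I error of the group × (over minus under) test.** Further assumptions: 67 per arm, two-sided 0.05, and correlation ρ between the over- and under-threshold means, each with unit SD. The difference then has SD √[2(1 − ρ)].

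| Fade L | ρ | Average over random shared orders | At D = 5 positions |
|---|---|---|---|
| 25% | 0.5 | 0.052 | 0.057 |
| 25% | 0.9 | 0.060 | 0.087 |
| 50% | 0.5 | 0.058 | 0.079 |
| 50% | 0.7 | 0.063 | 0.099 |
| 50% | 0.9 | 0.089 | 0.201 |
| 100% | 0.5 | 0.081 | 0.170 |
| 100% | 0.9 | 0.201 | 0.610 |

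**6. Group contrasts.** Both arms receive the same sequence. At any one level, position and preceding stimulus are therefore identical in the two arms, and so they are pooled over levels. The randomised comparison has no order bias in either form.

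**The case against.** The strongest reply is that the premise is unproven. The pilot sentence goes on to speak of individual calculation, the article also uses the phrase across participants for orders that do vary between people, and the app's output is not shown. This stands as a caveat: the shared sequence is a reading, not a fact. If the authors meant individual orders, the sentence still needs rewording.

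A second reply is that the planned comparisons are untouched. This also stands. Hypothesis 1, the primary outcomes and the sample size all concern a group difference. Under versus over threshold is a motivating question, not a listed hypothesis. A common order even has a merit for that group difference, since order effects are the same for everyone.

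A reader might go further and infer that level and time cannot be separated at all, so that the under-versus-over question is unanswerable. The documents do not support that. Each level occurs at three positions, and in a random order level explains on average only 4/14 (29%) of the variance in position. Trial-level ratings can therefore be modelled with both. The randomised block order also varies absolute time since training, though not position within the block. The sequence itself is not given and may be well balanced.

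Sensitisation, habituation or contrast that is equal in both arms cancels in every group comparison. These matter here only if they differ by arm, which nothing in the article shows.

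**Conclusion.** The point holds in a limited form. If the sequence is shared, as most naturally read, level is partly confounded with within-block position and preceding stimulus. The group-by-level comparison can then be distorted if training fades during the block or if order effects differ by arm. Hypothesis 1 and the primary group contrasts are not biased, and N = 134 is unaffected.

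On average the size is modest. Under an assumed 50% linear fade, the false difference is about 7% of the initial effect (15% at the 90th percentile), and the average type I error is about 0.06 to 0.09 for correlations of 0.5 to 0.9. It becomes large only with stronger fading or an unlucky sequence. The fade, the correlations and the equal true effect across levels are assumptions, and the actual sequence is unknown. Because correction is cheap and the comparison is the stated reason for using the thermal analyser, it should be made.

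**What to change.** In the main-study ISSA section, and for the heat block carried over from the pilot, state that the 15 trials are newly randomised for each participant and each block, generated in the same way in both arms. Three mini-blocks, each containing all five levels once, would be better still. Within a mini-block the over-minus-under imbalance has variance 2.5 × (1/2 + 1/2) = 2.5, so over three mini-blocks the SD is √(2.5/3) = 0.91 positions instead of 2.58. Record trial number.

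For participants already tested under a shared order, analyse group-by-level from trial-level ratings in a mixed model with trial position, its interaction with group, and the previous level.

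The change needs no extra participants or testing time. The operator must enter a different sequence for each participant. If the change comes after the study has started, the data set will mix two order regimes. The stated start date is 1 June 2024, so this is likely and should be reported. If orders are already individual, one clarifying sentence is enough.

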Based upon these findings and results from the broader literature, the following modifications have been made to the experimental protocol for the main investigation. First, the primary outcome of interpretation of ambiguous somatosensory sensations will be performed immediately following CBM-I, with assessment of post CBM-I cognitive biases performed after this. This will eliminate the possibility that assessing post-CBM-I cognitive biases reduces the training effect. Second, assessments of pain-related attentional bias and memory bias will also be conducted following CBM-I. Pain-related biases in attention (e.g., [57–68]) and memory (e.g., [45,69–74] have been frequently explored by our research group and others across a range of populations and using a range of paradigms, and their inclusion in the protocol will enable an assessment of the inter-relatedness of different forms of cognitive bias as predicted by theoretical models such as the Threat Interpretation Model of Pain [75] and the Integrated Contextual-Functional Framework [76]. Third, due to the small between-groups effect size (*d* =  -0.05) in the pilot study, the Incidental Learning Task will not be included (and which will provide time for assessments of attentional and memory bias). Fourth, in addition to ambiguous hot sensations, an assessment of interpretation of ambiguous cold sensations will also be conducted, as research suggests people are more sensitive to cold stimuli than hot stimuli [77,78], perhaps due to a greater overall density of cutaneous cold thermoreceptors than warm receptors [79]. Fifth, research has suggested intolerance of uncertainty is associated with higher experimental pain intensity ratings [80]. The Intolerance of Uncertainty Scale-12 Item [81] measure will therefore be added to the questionnaire battery in order to explore associations between intolerance of uncertainty and interpretation of ambiguous somatosensory sensations.

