### Primary and secondary outcomes

The primary outcomes in this study are pain intensity and unpleasantness for ambiguous somatosensory sensations as assessed via the ISSA paradigm. Secondary outcomes are (i) pain-related interpretation biases for ambiguous words and scenarios as assessed via the Ambiguous Scenarios Task and Sentence Generation Task respectively, (ii) pain-related attentional and memory biases as assessed via the visual-probe task and surprise free-recall task respectively, and (iii) anxiety (State-Trait Anxiety Inventory), depression (Beck Depression Inventory-II), anxiety sensitivity (Anxiety Sensitivity Index-3), somatosensory amplification (Somatosensory Amplification Scale), pain catastrophising (Pain Catastrophising Scale), intolerance of uncertainty (Intolerance of Uncertainty Scale-12 Item), and handedness (Edinburgh Handedness Questionnaire – Short Form).

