Descriptive statistics will be computed for demographic characteristics, self-report measures (scored according to their instructions), cognitive bias task scores (Ambiguous Scenarios Task test phase, Sentence Generation Task, Visual-Probe Task and free recall task) and responses on the Interpretation of Ambiguous Somatosensory Sensations Task. Differences between the benign and pain modification groups will be conducted using independent samples *t*-tests and mixed-design ANOVAs where appropriate. Should any statistically significant differences be observed between groups on demographic or self-report measures, analyses will be conducted controlling for these (e.g., Analysis of Covariance). Pearson’s correlation coefficients will be conducted between outcomes on the self-report measures, cognitive bias scores and interpretation of ambiguous sensations ratings. As thermal pain sensitivity is associated with age (e.g., [88–90]), Pearson’s correlation coefficients will also be computed between age and interpretation of ambiguous sensations ratings. Should these be statistically significant, then age will be controlled for as a covariate where appropriate in the statistical analyses. The moderating effects of visual imagery and intolerance of uncertainty on the association between group and interpretation bias scores from the Ambiguous Scenarios Task will be investigated using linear multiple regression models. Similarly, linear multiple regression models will be used to test the effect of group on interpretation bias measures while controlling for other variables that differ between groups.

Data from the Ambiguous Scenarios Task, Sentence Generation Task and ISSA will be processed as discussed above for the pilot study. The only difference is that for the Sentence Generation Task, two raters will independently and blindly categorise participant response sentences as either pain-related (e.g., *He had a pressing pain in his head*) or benign (e.g., *The boy was pressing the buttons in the lift*). The initial inter-rater agreement will be computed, and any disagreements between raters will be discussed in order to reach consensus (involving a third independent member of the research team if necessary).

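### Heat/cold block order is randomised in the ISSA but not mentioned in the analysis; adding it is a nearly free, low-priority gain for single-modality results

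*Protocol article*

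**What the plan says.** The main-study ISSA section adds a block of fifteen cold trials to the fifteen heat trials and fixes their sequence as follows: "The order of heat and cold pain trials will be randomised across participants". A three-minute break without the thermode separates the two blocks. Heat-first versus cold-first is therefore a two-level, randomised, between-participant factor inside the primary task. The section on primary and secondary outcomes confirms its status: "The primary outcomes in this study are pain intensity and unpleasantness for ambiguous somatosensory sensations as assessed via the ISSA paradigm".

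The main-study section on data reduction and analysis says that group differences "will be conducted using independent samples *t*-tests and mixed-design ANOVAs where appropriate". The factors of those ANOVAs are not listed; stimulus level and modality are not named either. Two routes to adjustment are given. The first is "Should any statistically significant differences be observed between groups on demographic or self-report measures, analyses will be conducted controlling for these". The second concerns age: if it correlates significantly with the ratings, "then age will be controlled for as a covariate where appropriate in the statistical analyses". ISSA data are to be processed as in the pilot, which had heat trials only and so had no block order to handle.

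The section on insights from the pilot explains why the ISSA now directly follows training: "This will eliminate the possibility that assessing post-CBM-I cognitive biases reduces the training effect".

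**The concern.** For either modality, one part of the sample is rated straight after training. The rest is rated after fifteen trials of the other modality and a three-minute break. If ratings differ between the first and second block, through sensitisation, habituation, fatigue or growing familiarity with the scale, a single-modality analysis of group alone puts that difference into residual variance. A chance imbalance of order between arms would also add noise to the group difference.

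The trial generates this factor itself, knows it for every participant and can use it at almost no cost. The stated covariate rules cannot pick it up: order is neither a demographic nor a self-report measure, and it is not age. Even a marked chance imbalance in order would therefore trigger no adjustment under the rules as written.

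What is at stake is modest: some precision in heat-only and cold-only results and in any group-by-modality test, and a view of whether the group difference looks smaller in the second block.

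**Working it through.** **Inputs from the article** (main-study Participants and analysis sections): f = 0.244, two-sided alpha 0.05, power 0.80, numerator df 1, two groups, N = 134.

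**Input not in the article:** D, the difference between first-block and second-block ratings of one modality, in units of the total SD. It is an assumption, so a range is shown.

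**Step 1: reproduce the plan's figure.** Noncentral F with λ = N·f² = 134 × 0.244² = 134 × 0.059536 = 7.98, on 1 and 132 df, gives power 0.8006. At N = 133 it is 0.798. So 134 is correct, and order plays no part in it.

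**Step 2: cost of the term if there is no order effect.** With one more parameter (df 1 and 131) power is 0.80060 against 0.80065, a loss below 0.0001. With two more (df 1 and 130) it is 0.80056.

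**Step 3: gain for one modality if there is an order effect.** With orders split 1:1, order explains a share R² = D²/4 of the variance. Removing it raises the effect size to f/√(1 − R²). Power is at N = 134 on 1 and 131 df.

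| D (assumed) | R² = D²/4 | adjusted f | power with order | power without |
|---|---|---|---|---|
| 0.25 | 0.0156 | 0.2459 | 0.807 | 0.801 |
| 0.50 | 0.0625 | 0.2520 | 0.825 | 0.801 |
| 0.75 | 0.1406 | 0.2632 | 0.856 | 0.801 |

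**Step 4: type I error and the average over modalities.** A simulation used 67 per arm, 4,000 runs, an assumed heat–cold correlation of 0.5, group effect d = 2f = 0.488 and a common second-block shift of 0, 0.3, 0.5 or 0.8. Here the shift is in units of the SD within an order, so the comparison falls below 0.80 without the term instead of rising above it with the term.
- Type I error lay between 0.047 and 0.052 throughout, with or without order.
- Single-modality power at shift 0.5 was 0.777 without order and 0.800 with it; at 0.8 it was 0.742 and 0.795.
- For the mean of heat and cold, power was 0.89 to 0.90 at every shift, with or without order.

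The last result follows algebraically. Each participant has one modality in the second block, so a common shift δ adds δ/2 to everyone's average and cancels between arms. In the heat-minus-cold difference, which a group-by-modality test uses, the shift is +δ in one order and −δ in the other. The two orders then differ by 2δ, and this stays in the error term unless order is modelled.

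**Step 5: chance imbalance.** If orders are drawn independently, the heat-first count in each arm is Binomial(67, 0.5). The counts differ by more than 11 (11/67 = 16.4 percentage points) in about 5% of trials. At D = 0.5 an imbalance of that size moves a single-modality group difference by 0.164 × 0.5 = 0.08 SD, about one-sixth of 0.488. Independent draws are an assumption, since the article does not say how order is allocated; balanced allocation would make the imbalance smaller.

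**The case against.** The strongest objection is that order is unmentioned, not excluded. A mixed-design ANOVA needs a within-subject factor and none is named, so the article plainly does not list its model terms. Such terms are often left to a fuller plan that is not shown. This stands, and it rules out saying that the plan deliberately analyses group alone or assigns per-modality t-tests to the ISSA. What remains is that the article does say when covariates enter, and neither rule reaches the one design factor randomised within the primary task.

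A reader might also infer that removable variance certainly sits in the primary outcomes. The documents do not support that. They give no order effect, and the primary outcomes are intensity and unpleasantness without separation by modality. In a contrast averaged over heat and cold, a common shift cancels.

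A reader might infer bias from chance imbalance of order. There is none: order is randomised, the imbalance is ordinary sampling variation, and the standard error already covers it.

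Finally, a reader might take the reason for moving the ISSA forward as proof that the protocol expects block position to matter. That passage speaks only of a possibility and concerns cognitive-bias tasks, not thermal trials. Waning of training would be a group-by-order interaction. If the arms converged symmetrically, the order main effect would be zero and the D²/4 formula would not describe it. The power figures therefore do not measure waning.

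**Conclusion.** The point holds as a free improvement of low priority. Block order is randomised, is not mentioned in the analysis and would not enter under the stated covariate rules. There is no bias, no inflation of type I error and no fault in N = 134.

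The benefit is conditional on a real order effect and on an analysis within one modality or of group by modality. For one modality, the gain is about 0.6, 2.5 and 5.6 percentage points of power for assumed shifts of 0.25, 0.5 and 0.75 SD. For the average over heat and cold, it is nil under a common shift; only an order effect that differs between heat and cold would leave something to remove.

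**What to change.** State in the analysis section, before group-level results are seen, that block order (heat first or cold first) is a between-subjects factor in the ISSA mixed ANOVAs. In models with modality as a within-subject factor, keep the order-by-modality term, because a common block shift appears there. Where one modality is analysed alone, use a model with group and order instead of a t-test. Report group-by-order descriptively only: with about 33 participants per cell (134/4 = 33.5) it is no basis for a formal claim that training wanes.

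The cost is a sentence in the plan, one more factor in SPSS and one or two degrees of freedom, which take less than 0.0001 off power if order has no effect. No new data and no change to the design are needed.
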